### Blinding

This is a single-blinded study. Study outcomes will be evaluated by trained research assistants who are not aware of group allocation. Participants will not be told about the pattern of research allocation. During the intervention, blinding would be unveiled if serious complications and adverse events occur.

### Statistical methods

Exploratory data analysis and Shapiro-Wilk tests will be performed to determine the normality of data distribution. Continuous variables will be expressed as means with standard deviations or medians with interquartile ranges; mean differences will be expressed from baseline to the end of the study. For categorical variables, counts and percentages will be presented, and between-group comparisons at baseline will be tested with the *x*^*2*^ test [25]. Between-group differences at baseline, and in the change from baseline to the end, will be tested with repeated measure analysis of variance. An analysis of covariance will be used to adjust for baseline cognitive functioning. Paired *t*-tests will be performed for between-group comparisons from the baseline to the end. The level of significance will be set as a two-sided *P* value less than 0.05. Data analysis will be conducted using SPSS version 20.0 with intent-to-treat analysis (ITT) and per-protocol (PP) analysis. The results of the ITT analysis will be compared with those of the PP analysis to determine the consistency.

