### Interventions

Participants will be randomly allocated to either the SST group or the control group. The flow chart of this study was presented in Fig. 1*.* Participants in the control group will receive routine dysphagia care, while the intervention group will receive SST based on routine care five times a week for four weeks. The process includes five sections of swallowing muscles, and each section will provide step-by-step training, according to the difficulty experienced by the participant. Each section will be divided into three levels of difficulties, starting from level 1(easy) through level 2 to level 3 (difficulty) each time. As presented in Fig. 2, the instructional video will be shown to the patient along with one-to-one guidance.

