### Outcomes

Study outcomes will be evaluated by trained research assistants who are not aware of group allocation. The time points for measurement will be at baseline (*T*_1_, day 0), 2 weeks after intervention (*T*_2_, day 14), and 4 weeks after intervention (*T*_3_, day 28). The schedule of outcome measurement is presented in Fig. 3.

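### Repeated-measures ANOVA is assigned to the baseline difference and to the change to the end: its group term does not test the first, and its three-visit interaction is not the second

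*Protocol article*

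**What the plan says.** The Statistical methods section names one method for two hypotheses on the continuous measures: "Between-group differences at baseline, and in the change from baseline to the end, will be tested with repeated measure analysis of variance". Categorical variables are dealt with separately: "between-group comparisons at baseline will be tested with the *x*^*2*^ test".

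The Outcomes section sets three visits. "The time points for measurement will be at baseline (*T*_1_, day 0), 2 weeks after intervention (*T*_2_, day 14" gives the first two, and "4 weeks after intervention (*T*_3_, day 28" gives the last. They are 14 days apart.

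Two further analyses are named in the same section: "An analysis of covariance will be used to adjust for baseline cognitive functioning" and "Paired *t*-tests will be performed for between-group comparisons from the baseline to the end". The article does not say which visits enter the ANOVA, or which of its terms answers which question.

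**The concern.** The sentence states two null hypotheses: no difference between arms at T1, and no difference between arms in T3 minus T1. A repeated-measures ANOVA on T1, T2 and T3 has two standard terms involving group, and neither omnibus term has one of these as its null. The group term compares means averaged over the visits. The group-by-time term asks whether the two profiles are parallel across all three visits.

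Two misreports could follow. An effective training programme could be reported as a baseline imbalance in a randomised trial. A difference confined to T2 could be reported as a difference in change to the end. The sentence matters because SSA, one of the two primary outcomes, and the scale-score secondary outcomes (AEBQ, MNA, Barthel Index) are analysed under it. The mismatch does not depend on missing data or on the choice of covariates.

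**Working it through.** The sentence contains no figure to reproduce, so the check asks what each ANOVA term tests and how often it rejects.

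**Inputs from the article.** Two-sided alpha 0.05; 1:1 allocation; 100 recruited, so n = 50 per arm; 20% attrition, so 100 × 0.8 / 2 = 40 per arm; three visits.

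**Assumptions.** The article gives no SD, correlation or effect size for SSA. I take normal scores, SD 1, the same correlation ρ = 0.5 or 0.7 between any two visits, and complete data on n per arm. Let d1, d2, d3 be the between-arm differences in SD units at T1, T2, T3, and d̄ their mean.

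**Noncentrality of each F test**
- Group term, three visits: (n/2) d̄² / [(1 + 2ρ)/3], on 1 and 2n − 2 df.
- Group-by-time, three visits: (n/2) Σ(dj − d̄)² / (1 − ρ), on 2 and 2(2n − 2) df.
- T3 minus T1 change: (n/2)(d3 − d1)² / [2(1 − ρ)], on 1 and 2n − 2 df.
- Baseline comparison: (n/2) d1², on 1 and 2n − 2 df.
- T3 adjusted for the baseline value, when d1 = 0: approximately (n/2) d3² / (1 − ρ²), on 1 and 2n − 3 df.

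**Step 1: the group term as a baseline test.** Take arms equal at baseline (d1 = 0).
- Effects (0, 0.3, 0.6), d̄ = 0.3. Smallest case, n = 40, ρ = 0.7: 20 × 0.09 / 0.8 = 2.25, rejection 31.6%.
- Effects (0, 0.6, 0.6), d̄ = 0.4. Largest case, n = 50, ρ = 0.5: 25 × 0.16 / 0.667 = 6.00, rejection 67.9%.
- A direct baseline test has noncentrality 0 and rejects 5%.
- Entering only T1 and T3 does not cure this. With d3 = 0.6, d̄ = 0.3 and variance (1 + ρ)/2, the noncentrality is 20 × 0.09 / 0.85 = 2.12 (30.1%) to 25 × 0.09 / 0.75 = 3.00 (40.3%).
- It also fails the other way. With differences (0.5, 0, −0.5), d̄ = 0 and the group term rejects 5%. A direct baseline test at n = 50 has 25 × 0.25 = 6.25 and rejects 69.7%.

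**Step 2: the three-visit interaction as a test of change to the end.** Take (0, 0.5, 0), so T3 minus T1 is the same in both arms. Here d̄ = 0.167 and Σ(dj − d̄)² = 0.167.
- n = 40, ρ = 0.5: 20 × 0.167 / 0.5 = 6.67, rejection 62.4%.
- n = 50, ρ = 0.7: 25 × 0.167 / 0.3 = 13.89, rejection 92.2%.
- The T3 minus T1 test has noncentrality 0 and rejects 5%.

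| Term and effects (T1, T2, T3) | n=40, ρ=0.5 | n=40, ρ=0.7 | n=50, ρ=0.5 | n=50, ρ=0.7 |
|---|---|---|---|---|
| Group term (0, 0.3, 0.6) | 36.8% | 31.6% | 44.4% | 38.2% |
| Group term (0, 0.6, 0.6) | 58.1% | 50.6% | 67.9% | 60.0% |
| Interaction (0, 0.5, 0) | 62.4% | 84.9% | 72.9% | 92.2% |
| Interaction (0, 0.3, 0.6) | 66.0% | 87.7% | 76.4% | 94.1% |
| T3 − T1 change (0, 0.3, 0.6) | 75.5% | 92.8% | 84.4% | 97.0% |
| T3 adjusted for baseline (0, 0.3, 0.6) | 86.4% | 96.0% | 92.9% | 98.6% |

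Simulations of 8,000 trials per scenario agree with these rates to within about one percentage point.

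**Step 3: when the ANOVA does test the change.** With T1 and T3 only, Σ(dj − d̄)² = (d3 − d1)²/2. The interaction then has the same noncentrality and degrees of freedom as the change test; in simulation its F equalled the squared change-score t exactly. With three equally spaced visits, the linear contrast has weights −1, 0, +1, so its group comparison is also exactly T3 minus T1.

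**Step 4: no effect at any visit.** Every noncentrality is 0, so every term rejects about 5%.

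**Step 5: the other named analyses.** The covariance analysis is stated only for baseline cognition, not for the baseline value of the outcome. A paired t-test compares measurements within a person and cannot compare two independent arms. Neither supplies a clearly specified 1-df between-group test of the change.

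**The case against.** The strongest reply is that the sentence is loosely worded rather than wrong. It names the quantity of interest, and a repeated-measures ANOVA can test that quantity exactly in the two ways shown in Step 3. Which term is read could be left to an analysis plan. This stands in part. A reader might infer that no term or contrast of the ANOVA can test the change to the end, and the article does not support that. It does not say that all three visits enter, nor that the omnibus interaction will be the term read.

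The second reply is that a false end effect needs a benefit at T2 that has gone by T3. That is correct: without any effect, error stays near 5%, and under a sustained effect the interaction behaves much like the change test. On one reading the pattern is also unlikely, because "the intervention group will receive SST based on routine care five times a week for four weeks" would place T3 at the end of training. But the Abstract calls T3 follow-up, and the Data collection section calls T2 the intervention period. Those passages need to be reconciled, and the pattern cannot be ruled out meanwhile.

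The third reply is that no stated decision depends on a baseline p-value, so a mislabelled one does limited harm. This limits the consequence but does not make the group term a baseline test under any choice of visits.

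A reader might also infer that most of the power is lost if the group term is taken as the treatment test. That holds only in some scenarios, and under a reading that the article does not state. With (0, 0.6, 0.6), n = 50 and ρ = 0.5, the group term has 67.9% against 84.4% for the change test.

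Finally, the trial is labelled exploratory. It nevertheless aims to evaluate effectiveness and sets a two-sided 5% level, so the test and its hypothesis should match.

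**Conclusion.** The point holds, in two parts of different strength. The baseline part holds whichever visits are entered: the group term is not a baseline test, and under the assumed effects it rejects in about 32% to 68% of trials with equal baselines. The change part is conditional. If all three visits enter and the omnibus interaction is read, a 0.5 SD effect at T2 alone gives significance in about 62% to 92% of trials with no difference in change to T3. If T1 and T3 alone enter, or the linear contrast is read, the stated hypothesis is tested exactly.

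This is not a general inflation of type I error. The sizes rest on assumed effects, correlations and a common SD; the direction follows from the definitions of the terms. The point concerns SSA and the scale scores, not the WST effective rate. It should be corrected because nothing else in the section clearly supplies the right test and the repair is almost free.

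**What to change.** Replace the sentence with: *The treatment effect on SSA and the other scale scores is the 1-df between-group difference at T3 adjusted for the baseline value of the same score (alternatively the 1-df contrast in T3 minus T1 change), with its 95% CI. The T2 contrast is supportive. The overall group term and the omnibus group-by-time term are not used to claim an effect at the end.* One of the two forms should be chosen before the data are seen. Describe baseline by arm with summaries, not with repeated-measures ANOVA.

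An unadjusted comparison at T3 is not a good substitute. It is not the stated change hypothesis, and for a 0.6 SD effect its power is 75.5% (n = 40) or 84.4% (n = 50) whatever the correlation. At ρ = 0.7 the change contrast has 92.8% and 97.0%. The baseline-adjusted comparison does better than both (table above), and because randomisation makes expected baselines equal, it estimates the same effect as the change contrast.

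The cost is one sentence of text and one contrast or covariate, using data already planned. The downside is that an effect seen only at T2 no longer counts as an effect at the end.

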### Sample size

The sample size was calculated based on the comparison of WST. By using G*Power 3.1 software, we set a significant difference of 14.2% (74.2% in the experimental group and 60.0% in the control group), an alpha error of 0.05, a beta error of 0.80, and the effect size *f* = 0.32. After calculation, a total sample size of 78 was required. To accommodate for a 20% attrition rate and other confounding factors, we recruited 100 participants. After obtaining informed consent, each involved hospital was allocated to the intervention group or to the control group in a 1:1 ratio.

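### Unless missing values are imputed first, repeated-measures ANOVA would run the ITT analysis on completers, and testing change without adjusting for the outcome's own baseline gives up precision

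*Protocol article*

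**What the plan says.** All of the analysis choices at issue stand in the protocol article under Statistical methods.

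- Main test: "Between-group differences at baseline, and in the change from baseline to the end, will be tested with repeated measure analysis of variance".
- Covariate: "An analysis of covariance will be used to adjust for baseline cognitive functioning". No other covariate is named, neither the outcome's own baseline score nor hospital.
- Analysis sets and software: "Data analysis will be conducted using SPSS version 20.0 with intent-to-treat analysis (ITT) and per-protocol (PP) analysis".
- Use of the two sets: "The results of the ITT analysis will be compared with those of the PP analysis to determine the consistency".

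Under Sample size, the article states its expectation of loss: "To accommodate for a 20% attrition rate and other confounding factors, we recruited 100 participants". Under Outcomes, it sets three measurement times: T1 (day 0), T2 (day 14) and T3 (day 28). The article names no imputation, mixed model or other means of keeping a participant with a missed visit in the ITT analysis. A fuller protocol or an SAP, not shown, may do so.

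**The concern.** The named test and the named analysis set pull against each other. Classical repeated-measures ANOVA, as in the SPSS general linear model for repeated measures, needs a value at every level of the repeated factor and removes any participant who lacks one. The paired t-tests in the same section also need both values. An ITT label on such a run would then describe randomised participants who happened to be complete. If those lost differ from those who stay, and differ between arms, the estimated SST effect can shift. Agreement between ITT and PP would not reveal this, because both runs would leave out the same dropouts.

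The second matter is precision. Every scored outcome is measured at T1, yet the ANOVA uses that value only by testing change from it, and the ANCOVA is described as adjusting for cognition. Adjusting for the T1 score uses the same data better, which matters in a trial of 100.

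**Working it through.** **Inputs.** From Sample size: "an alpha error of 0.05, a beta error of 0.80, and the effect size *f* = 0.32" (the 0.80 is read as power), 78 required, 20% attrition and 100 recruited. From Statistical methods: two-sided 0.05. Assumed, not in the documents: correlations between visits, equal SDs at all visits, and the rates and mechanism of missed visits.

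**1. The plan's own figures.** With two groups, d = 2f = 0.64, so n per arm = 2(1.96 + 0.84)²/0.64² ≈ 38.3, rounded up to 39, or 78 in total. The noncentral F test gives 80 and a chi-square with w = 0.32 gives 77, so 78 reproduces from f = 0.32. Attrition: 78/0.80 = 97.5, rounded up to 98, against 100 recruited. This allowance treats dropouts as contributing nothing. (Whether f = 0.32 matches the response rates quoted beside it is a separate question and is not used here.)

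**2. Who stays in a complete-case ANOVA.** With 20% attrition and no other missed visits, 100 × (1 − 0.20) = 80. If T2 and T3 can be missed independently, at assumed rates:

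| Missed T2 | Missed T3 | Complete of 100 |
|---|---|---|
| 10% | 10% | 81 |
| 10% | 20% | 72 |
| 20% | 20% | 64 |

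If the ANOVA used only T1 and T3, a missed T2 alone would remove nobody.

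**3. Power.** Taking f = 0.32 at face value for a two-group comparison, with noncentrality N × f²: N = 100 gives 10.24 and power 0.887; N = 80 gives 8.19 and power 0.807. The loss at 20% is therefore already allowed for in the sample size. At 80 analysed, the planned power is kept.

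**4. Bias.** A simulation assumed 50 per arm, SD 1, a true T3 effect of −0.64 (half of it at T2) and 4,000 runs, and analysed the T1-to-T3 change in completers. T3 was lost in about 20%. In the informative case, loss in the SST arm rose with a worse T2 score and was random in the control arm.

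| Correlations T1-T2, T1-T3, T2-T3 | Random loss, estimate | Informative loss, estimate | Informative loss, no true effect: shift | Type I error |
|---|---|---|---|---|
| 0.6, 0.6, 0.6 | −0.641 | −0.640 | 0.003 | 0.050 |
| 0.7, 0.5, 0.7 | −0.637 | −0.640 | −0.004 | 0.048 |
| 0.5, 0.3, 0.7 | −0.639 | −0.688 | −0.040 | 0.048 |
| 0.5, 0.4, 0.8 | −0.636 | −0.717 | −0.073 | 0.062 |

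The completer estimate is unbiased under random loss. Under informative loss it is also unbiased when T2 is as strongly related to T1 as to T3 (first two rows). It drifts by up to about 0.08 SD in favour of SST when T2 is closer to T3 (last two rows). A regression of T3 on T1 and T2 within arm, predicting for everyone, gave −0.640 to −0.643 in all four informative cases.

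**5. Precision.** With equal SDs and baseline-outcome correlation ρ, the variance is proportional to 2(1 − ρ) for a change score and to 1 − ρ² after adjustment for baseline. The ratio is (1 + ρ)/2.

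| ρ (assumed) | Change | Adjusted | Ratio | Cut |
|---|---|---|---|---|
| 0.3 | 1.40 | 0.91 | 0.65 | 35% |
| 0.5 | 1.00 | 0.75 | 0.75 | 25% |
| 0.7 | 0.60 | 0.51 | 0.85 | 15% |

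**The case against.** The strongest reply is that a journal article condenses the plan. It commits to ITT, and imputing before the ANOVA would honour that commitment without contradicting a word of the text. Handling of missing values is commonly left to an SAP. This stands: the reduction to completers is conditional, and the article's silence on missing values is not itself the fault. What remains is that the named test keeps incomplete participants only with an added step, while a readily available alternative uses their observed visits directly.

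The 20% is a planning allowance, not a count of exclusions. Discharged participants are also to be followed by telephone or WeChat, partly to secure measurements, so actual loss may be lower. The trial is labelled exploratory. These points limit the likely size.

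Several stronger readings are tempting but not supported:

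- A reader might infer that the ITT and PP sets would be nearly identical. The article does not define PP, and it records attendance as adherence. A fully assessed participant with poor attendance could be excluded from PP only.
- A reader might infer that baseline imbalance goes uncorrected. T1 is a level of the repeated factor and change from it is tested. That handles imbalance less well than adjustment does, but does not ignore it. Not adjusting does not in itself bias a randomised comparison.
- A reader might quote the larger gain of 1 − ρ² against an unadjusted T3 comparison. The plan makes no such comparison, so change scores are the right reference.
- A reader might call the absence of hospital from the models an error. No stratified randomisation is stated, so a hospital term is an optional gain in precision.

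**Conclusion.** The point holds in a conditional form. If nothing is imputed first, about 80 of 100 randomised participants would enter the ITT run at the article's own attrition figure, and agreement with PP would say little about attrition. Bias is not established. It ranged from none to about 0.08 SD in the simulated cases and depends on a dropout mechanism that the documents do not give. Planned power is not undermined at 20% loss.

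The precision point does not depend on missing data. Adjusting for the T1 score cuts the variance by 25% to 15% against change scores at an assumed correlation of 0.5 to 0.7. This concerns efficiency, not validity.

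The conclusion applies to the scored outcomes and assumes that participants are the unit of allocation, as described under Interventions. The Sample size section can be read as allocating whole hospitals. If that were so, hospital and treatment would be confounded and no covariate could separate them.

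**What to change.** For SSA, AEBQ, MNA and BI, replace the repeated-measures ANOVA and the cognition-adjusted ANCOVA with one linear mixed model, which SPSS can fit:

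- outcomes: the T2 and T3 scores, with an unstructured covariance;
- terms: arm, visit, arm-by-visit, the outcome's own T1 score and baseline MMSE, with hospital optional;
- participants: all randomised with any post-baseline value, analysed as randomised;
- result: the arm difference at T3 with its 95% CI, with PP kept as a sensitivity analysis.

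Two limits should be written in. Participants with no post-baseline value still drop out of this model, so state an imputation or a sensitivity analysis for them. The WST effective rate is binary and needs its own model.

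The cost is a change of wording and slightly more analysis work in the same software, with no new data. The model assumes that values are missing at random given the observed scores and covariates, and the plan should say so.

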## Methods

### Trial design

This training program is a multi-center, exploratory, single-blinded, parallel randomized controlled trial (RCT) with a 4-week follow-up period. All stages are conducted according to the SPIRIT reporting guidelines [18]. Treatments administered will be allocated randomly according to a 1:1 ratio by an online random-number generator of SPSS software by research assistants who are not involved in assessment and intervention. The researcher will then offer the research assistants in each hospital the allocation of groups with sequentially numbered opaque, sealed, and stapled envelopes. Then, the training schedule will be conducted based on this research protocol.

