#### Primary outcomes

Water Swallowing Test (WST), a five-level water drinking test, will be used to determine the effectiveness of SST. Evaluators observed individual reactions after drinking 30 ml of water (complete recovery: swallowing without cough; improved swallowing function: occasional choking, and invalid: unchanged or worse swallowing function). Effective rate = (completed recovery + improved swallowing function)/total cases in each group *100%. The sensitivity and specificity of WST ranged from 34.8 to 55.7% and 78.9 to 93.2% in older adults [20].

On basis of WST, Standard Swallowing Assessment (SSA) will be performed to evaluate the severity of dysphagia. The score of SSA ranged from 18 to 46, and a high SSA score reflected serious dysphagia. SSA exhibited a specificity of 0.90 and a sensitivity of 0.97 in detecting dysphagia, with positive and negative predictive values of 0.92 and 0.96 [21].

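### Paired t-tests are assigned to the between-group comparison of two unmatched arms; they test change within an arm, and the article does not say that the valid between-arm tests decide instead

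*Protocol article*

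**What the plan says.** Three sentences of the Statistical methods section bear on the treatment comparison of the scale scores.

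- Repeated-measures ANOVA: "Between-group differences at baseline, and in the change from baseline to the end, will be tested with repeated measure analysis of variance".
- ANCOVA: "An analysis of covariance will be used to adjust for baseline cognitive functioning".
- Paired t-test: "Paired *t*-tests will be performed for between-group comparisons from the baseline to the end".

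The Trial design section describes a "multi-center, exploratory, single-blinded, parallel randomized controlled trial (RCT) with a 4-week follow-up period" and says "Treatments administered will be allocated randomly according to a 1:1 ratio". The article mentions no matching of patients across arms. Significance is two-sided at 0.05. Nothing in the section ranks the three procedures or names one as the basis for the conclusion about SST.

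**The concern.** A paired t-test needs two linked observations per unit. Patients in different arms of this trial are not linked, so the test cannot do what the sentence assigns to it. If it is run on each patient's baseline and end values, it asks whether an arm changed, which is a different question from whether SST changed patients more than routine care did.

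The difference matters in this design. Controls receive routine dysphagia care, so change is plausible in both arms. Entry requires a third-degree or worse Water Swallowing Test, and that test is also a primary outcome, so some regression to the mean is to be expected on it. A within-arm test credits SST with routine care, natural change and regression to the mean together. If such a P value were reported as the between-group result, the benefit of randomisation would be lost for that result.

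**Working it through.** **1. What the plan's own sample size assumes.** The Sample size section gives f = 0.32, alpha 0.05, a figure of 0.80 printed as the beta error (read here as power), and 78 patients. For two groups d = 2f = 0.64. Per arm, n = 2(1.960 + 0.842)²/0.64² = 15.70/0.4096 = 38.3, rounded up to 39, so 78 in total. The exact F calculation gives 80, with power 0.797 at 78. The 78 is therefore reproduced by a comparison of two independent groups, not by a paired test.

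**2. What a paired t-test can measure here.** There are two ways to run it.

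- *Within an arm.* With mean change δ and SD of change σ, the noncentrality is (δ/σ)√n. It depends on the change in that arm alone; the other arm does not enter.
- *Across arms, pairing unrelated patients.* The false-positive rate stays near 5% (4.9% to 5.1% in the simulation below at 39 per arm, with change of 0.25 to 0.75 SD). But the P value then depends on the arbitrary order in which patients are listed, the arms must be of equal size, and the degrees of freedom fall from 76 to 38. No analyst would intend this.

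**3. Illustration.** Assumptions, none of them from the article: normally distributed change, no SST effect, and the same true change in both arms of 0.25, 0.5 or 0.75 SD of change. There were 20,000 simulated trials per setting. At 39 per arm (√39 = 6.245):

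| Equal change in both arms (SD) | Noncentrality | SST-arm paired test P < 0.05 | SST significant, control not | Independent t-test on change P < 0.05 |
|---|---|---|---|---|
| 0.25 | 1.56 | 33% | 22% | 5.0% |
| 0.50 | 3.12 | 86% | 12% | 5.0% |
| 0.75 | 4.68 | 99.5% | 0.4% | 5.1% |

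The fourth column can be checked by hand. With independent arms and within-arm power p, it is p(1 − p): 0.33 × 0.67 = 0.22; 0.864 × 0.136 = 0.12; 0.995 × 0.005 = 0.005. At 50 per arm the paired test is significant in 41%, 94% and 99.9% of trials, and the independent test again in about 5%.

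The third and fourth columns describe different misuses, and they do not peak together. When change is large, both arms are nearly always significant, and the pattern of SST significant and control not almost disappears.

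**4. Where the WST stands.** The Primary outcomes section defines a responder proportion: "Effective rate = (completed recovery + improved swallowing function)/total cases in each group *100". The Sample size section plans on "a significant difference of 14.2% (74.2% in the experimental group and 60.0% in the control group"). These are percentages of patients, whereas a t-test compares means. The article gives no expected mean change in SSA, AEBQ, MNA or BI, which is why the range in step 3 has to be assumed.

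**The case against.** The strongest reply is that the valid analysis is already in the same section. Repeated-measures ANOVA is assigned to between-group differences in change, and an ANCOVA follows. Against that background the paired t-test sentence looks like a slip, for within-group or for independent-samples. The order of tests is often settled in an analysis plan that is not shown here, and the trial calls itself exploratory.

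Much of this stands. A reader might infer that the trial has no valid between-arm test; the article does not support that. What remains is that the sentence is wrong as printed and gives the paired test the same purpose as the ANOVA. The two likely corrections lead to different analyses, and the text does not show which was meant. As described, the ANCOVA adjusts for cognition and does not mention the baseline outcome score, so it does not clearly settle the matter. The exploratory label does not make a within-arm test comparative, and the stated aim is to evaluate effectiveness.

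Two further inferences go too far. A reader might assume within-arm power of 50% to 80% and quote a false-positive rate in favour of SST of 25% to 16% (0.5 × 0.5 and 0.8 × 0.2). That needs a rule declaring benefit when SST is significant and control is not. The article states neither that rule nor that power, and the range in the working runs from 22% down to 0.4%. A reader might also use the 60.0% planned for controls to predict how often the paired tests would be positive. Reading that figure as the WST effective rate is a reasonable inference, but it is a binary rate and does not size t-tests on the scale scores.

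**Conclusion.** The sentence is wrong as written. With unmatched parallel arms, a paired t-test supports statements about change within an arm and none about SST versus control. The defect is limited, because two between-arm analyses are also planned, but it is more than cosmetic, because the article does not say which procedure carries the conclusion and the invalid one could.

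Its size cannot be read from the article. Under the assumptions stated in the working, at 39 per arm with no SST effect, an SST-arm paired test read as evidence for SST would mislead in about 33% to 99.5% of trials, against about 5% for an independent test of change. Under the separate rule of SST significant and control not, the figure is about 22% down to 0.4%. Both ranges are conditional illustrations and not error rates of the planned analysis.

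**What to change.** Delete the paired t-test sentence, or relabel it: paired t-tests describe change within each group and carry no conclusion about SST.

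Then state what does carry the conclusion. For SSA, AEBQ, MNA and BI, the treatment effect is a between-arm estimate (SST minus control) with a 95% CI, taken from one of two analyses named in advance:

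- the group-by-time term of the planned repeated-measures ANOVA; or
- the planned ANCOVA at T3, with the baseline outcome score added alongside baseline cognition as covariates. The cognition adjustment is kept.

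Add that the WST effective rate is binary and is compared between arms as a difference in proportions with its 95% CI, not by a t-test.

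The cost is a few sentences of wording, settled before analysis. Baseline and T3 values are already scheduled, so no new data or patients are needed.
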